### RQ7 analyses: Intervention effect differences

The final set of hypotheses concern differences in any observed intervention effects. In particular, we hypothesize that the SEMLA and DIL intervention effects on a particular outcome measure will show greater variation for the SEMLA intervention than for the DIL intervention. These hypotheses will be tested by investigating whether the variance of the pre- and post-difference scores of the respective outcome measures significantly differ between the two intervention groups. This will be done using either Levene’s [105] or Brown and Forsythe’s [106] test of equality of variances.

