	SECDI	Age	Positive relationship	–	SECDI	Correlation / mixed model
	Preschool start	Other L1	Higher mean for Swedish L2 children	–	Preschool start	t-test / mixed-model
	Preschool time	SES	Positive relationship	–	Preschool time	Correlation / mixed model
	SES	Multilingual	Higher mean for Swedish L1 children	–	SES	t-test / mixed-model
	SECDI	SES	Positive relationship	–	SECDI	Correlation / mixed model
RQ7: Intervention effect differences	EF	SEMLA vs. DIL	Less variation in DIL	–	Selective attention difference, EF indice difference	F-test of variance equality
	Early Maths skills	SEMLA vs. DIL	Less variation in DIL	–	Maths difference	F-test of variance equality
	Socioemotional skills	SEMLA vs. DIL	Less variation in DIL	–	TEC difference	F-test of variance equality
	Communication	SEMLA vs. DIL	Less variation in DIL	–	Communication indice difference	F-test of variance equality
	Language	SEMLA vs. DIL	Less variation in DIL	–	Language indice difference	F-test of variance equality

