### Sample

#### Sample characteristics

The population consists of preschool children in the age range of 48 to 77 months, living in a municipality located in the eastern parts of the Stockholm metropolitan area. The sample consists of 432 children from 28 preschool units, which, in turn come from 18 preschools. Preschool units constitute clusters to which interventions are randomly assigned. Intervention assignment was constrained in the sense that units within the same preschool were always assigned either to the same intervention type or to one of the pedagogical interventions and the control group. From each preschool unit, a smaller group of children was randomly sampled (as described below) for participation in the ERP study. The size of these sub-samples was proportional to the size of the preschool unit from which they were drawn. The sample size in the ERP study is 123 individuals following attrition.

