The weaknesses connected to the project concern implementation of the study across preschools. Different engagement levels have been noted from different practitioners, and although the control preschools were enrolled in a self-evaluative assessment (BRUK) in the hopes of making them feel that they were actively involved in the study, there is a possibility that being assigned to the control condition in and of itself creates a sense of alienation from the project that could affect the outcome. The major obstacle observed throughout the project was, however, the different levels of participation found in different preschools as a result of particular individuals being more or less personally engaged in the tasks. Although this is a problem for a controlled study, it reflects the everyday situation of all educational practices. In the future, ways to measure and handle the “human aspect” of pedagogical reality as an influential factor in its own right need to be addressed. Thorough qualitative analysis of the interaction data from the present project could, in its continuation, contribute to a deepened discussion and knowledge of how we handle this influential but evasive reality.

The analysis methods chosen are ideal for analysing data sets such as the present one. In particular, by using mixed effects modelling it is possible to account for the hierarchical structure of the data, with children nested within preschool units, and preschool units nested within preschools. By including random slopes for each of these levels, the mixed effects models account for systematic variation that might exist between preschools or preschool units. The mixed effects model also allows for the inclusion of independent variables and covariates at different levels of nesting, such as the inclusion of interventions and the ECERS-3 scores on the preschool unit level, together with other covariates at the child level.

The results of the study are limited, containing outcomes from only 432 children of the approximately 500,000 attending Swedish preschools. However, the results carry the seed for a preschool setting based on evidence from a multifaceted investigation including considerations of children’s development through both measurable, quantitative test-scores on general abilities, and fine-grained qualitative analyses of skills not necessarily visible except through in-depth analyses of interactions between children and pedagogues.

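### RQ7 compares the spread of change scores between SEMLA and DIL with tests that treat children as independent, although preschool units were randomised

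*Protocol article*

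**What the plan says.** The RQ7 section of the protocol article asks "whether the variance of the pre- and post-difference scores of the respective outcome measures significantly differ between the two intervention groups", and the expected result in Table 1 is "Less variation in DIL". The test is given in two places:

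- RQ7 section: "This will be done using either Levene’s [105] or Brown and Forsythe’s [106] test of equality of variances".
- Table 1, all five RQ7 rows: "F-test of variance equality".

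Neither place mentions preschool units, preschools or any aggregation.

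On the design, the section on sample characteristics states: "Preschool units constitute clusters to which interventions are randomly assigned". It adds: "The sample consists of 432 children from 28 preschool units, which, in turn come from 18 preschools". Under Randomisation, allocations that put SEMLA and DIL in the same preschool were redrawn. The models for RQ1, RQ4 and RQ5 all carry random intercepts for unit and preschool, and RQ2 is tested within the RQ1 models. RQ7 is the one SEMLA-DIL contrast whose stated test has no such term.

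**The concern.** The F-test, Levene's test and the Brown-Forsythe test all take their null distribution from independent observations. Here children share a unit, staff and a preschool, and treatment was assigned to the whole unit. Two features of the clusters can make the arm variances differ by chance more than these tests allow: units may differ in mean change, or in how widely change scores spread within them.

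The article gives some reason to expect such differences. Its Discussion names as the major obstacle "different levels of participation found in different preschools as a result of particular individuals being more or less personally engaged in the tasks".

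At stake is a published statement that DIL acts more evenly across children than SEMLA, when a few preschools may simply have differed. The open choice between two tests, with a third label in Table 1, also leaves the analysis unfixed in an article that says it describes its procedures in advance to prevent fishing for results.

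**Working it through.** The article reports power for RQ1 to RQ5 only, so there is no stated RQ7 figure to reproduce.

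**Inputs from the article.** There are 432 children, 28 units and 18 preschools. That is 432/28 = 15.4 children per unit, 432/18 = 24 per preschool, 28/3 = 9.3 units per arm, and 18/3 = 6 preschools per arm if no preschool is split. Arm shares of 32, 36 and 32% give about 138, 156 and 138 children; the article does not say which share belongs to which arm. The ERP sample is 123 children, or 123/28 = 4.4 per unit. Alpha of 0.05 is stated for the power simulations and is taken as nominal here.

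**Inputs assumed.** ICC of the difference score: 0 to 0.20. Coefficient of variation (CV) of the within-cluster SD: 0 to 0.30. Scores are normal, and both arms have the same structure, so the null is true.

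**Why the child-level test fails.** The Brown-Forsythe score is z = |D − arm median|, where D is the difference score. With m children per cluster, the variance of an arm's mean z is (σ²_z/n) × [1 + (m − 1)ρ_z], where ρ_z is the ICC of z. The child-level test sets ρ_z to 0.

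If only the spread differs between clusters, normal scores give ρ_z = CV²(2/π) / [CV²(2/π) + (1 + CV²)(1 − 2/π)]. The true two-sided level is then approximately 2[1 − Φ(1.96/√DE)], where DE = 1 + (m − 1)ρ_z.

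- CV 0.15: ρ_z = 0.0143/(0.0143 + 0.3716) = 0.037. For m = 15, DE = 1.52 and the level is 11%. For m = 24, DE = 1.85 and the level is 15%.
- CV 0.25: ρ_z = 0.0398/(0.0398 + 0.3861) = 0.093. For m = 15, DE = 2.31 and the level is 20%. For m = 24, DE = 3.15 and the level is 27%.
- ERP measure, m = 4.4, CV 0.25: DE = 1.32 and the level is 9%.

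**Simulation.** 10,000 trials per row, two-sided at 0.05:

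| Layout per arm | ICC | CV | F | Levene | Brown-Forsythe | Cluster-mean t-test |
|---|---|---|---|---|---|---|
| 9 units × 15 | 0 | 0 | 0.048 | 0.049 | 0.048 | 0.048 |
| 9 × 15 | 0.10 | 0 | 0.063 | 0.064 | 0.062 | 0.048 |
| 9 × 15 | 0.20 | 0 | 0.110 | 0.107 | 0.104 | 0.047 |
| 9 × 15 | 0 | 0.1 | 0.085 | 0.076 | 0.073 | 0.047 |
| 9 × 15 | 0 | 0.2 | 0.223 | 0.170 | 0.165 | 0.056 |
| 6 preschools × 24 | 0 | 0 | 0.054 | 0.050 | 0.048 | 0.050 |
| 6 × 24 | 0.10 | 0 | 0.077 | 0.075 | 0.071 | 0.052 |
| 6 × 24 | 0.20 | 0 | 0.134 | 0.135 | 0.130 | 0.050 |
| 6 × 24 | 0 | 0.1 | 0.109 | 0.099 | 0.095 | 0.049 |
| 6 × 24 | 0 | 0.2 | 0.262 | 0.210 | 0.205 | 0.050 |

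Further Brown-Forsythe runs at intermediate values gave 11-17% for CV 0.15 (ICC up to 0.10) and 18-27% for CV 0.25, which agrees with the hand calculation.

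**Direction.** About half of the rejections point to less variation in DIL. That is 6-8% at CV 0.15, and 0.083 (9 × 15) or 0.107 (6 × 24) at CV 0.2, against 0.025 nominal.

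**The case against.** **The large figures rest on an input the article does not supply.** This stands. The Discussion speaks of engagement and participation, not of the spread of change scores. With equal spread and ICC up to 0.10 the inflation is minor. The layout of six preschools per arm is also near the unfavourable end, because a preschool may be split between one intervention and control, so an arm can include more than six.

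**The F-test label may be loose wording.** Levene's and Brown-Forsythe's tests are themselves F-tests on absolute deviations. A reader might infer that Table 1 plans the classical variance-ratio test and quote its higher error rates. Those apply only if Table 1 means that test, which the RQ7 section does not name. What remains is an unresolved choice. Levene and Brown-Forsythe behaved almost alike in simulation, so the choice between those two matters little.

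**A false RQ7 claim might be thought likely.** The article does not support that. The claim is directional. At CV 0.2 (9 × 15), six independent tests would give 1 − (1 − 0.083)⁶ = 41%. Six equal and independent tests also overstate the case: TEC is tested alone and is part of the communication composite, and the ERP measure has less inflation. The article openly limits p-value correction to RQ1 to RQ4, which is a separate matter.

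**Variation between units may be part of the target.** The RQ7 section says only that variation is greater in SEMLA, not that it is greater between children within a unit. This is fair. It concerns what is estimated, and it does not make the independence assumption valid.

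**Conclusion.** The point holds as a defect in a secondary analysis. The RQ7 p-values rest on independence between children, which the cluster design does not provide and which the RQ1, RQ4 and RQ5 models do not assume.

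The excess may be negligible or severalfold, depending on quantities that the article does not give. Differences in spread between clusters drive the larger figures; differences in mean change alone matter mainly at ICC near 0.20. The ranges assume normal scores and roughly equal clusters, and they describe plausible conditions, not estimates for this trial. Conclusions on mean intervention effects under RQ1 are not affected.

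**What to change.** Name one test, in the same words, in the RQ7 section and in the RQ7 rows of Table 1. For each outcome:

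1. Compute each child's absolute deviation of the difference score from the arm median.
2. Average it by cluster: by preschool, or by unit if variation at preschool level is negligible.
3. Compare SEMLA with DIL by a t-test on the cluster means.

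Deviations are taken from the arm median, so variation between units still counts towards the target. In simulation this test held 4-6%.

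A mixed model for the same score, with the RQ1 random intercepts and small-sample degrees of freedom, is an alternative. It was not simulated, and separating unit from preschool variance with 28 units in 18 preschools will be imprecise.

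The cost is a wording change in two places and one analysis per outcome on data already collected. RQ7 will show less apparent power, because the child-level tests overstate the information available when clusters differ.

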### Adjusting *P*-values for multiple comparisons

When multiple hypotheses are tested with inferential statistics, the risk for a false positive - falsely rejecting a null hypothesis in favour of the alternative hypothesis - goes up with the number of tests that are conducted. In other words, the risk for at least one type I error increases above the chosen alpha level with the number of tests that are conducted. In order to control for this alpha inflation when conducting multiple testing, some kind of *p*-value correction method is often employed. For the present analyses, we will use p-value correction for the *p*-values of the tests testing RQ1 to RQ4 hypotheses.

P-value correction will be done on the basis of the method proposed by Benjamini and Hochberg [107]. Instead of controlling the so-called familywise error rate, which is the probability of *at least one* Type I error, this method adjusts p-values for the so-called false discovery rate. The false discovery rate is the *expected proportion* of Type I errors (i.e., “false discoveries”) in a set of tests. Adjusting p-values for the false discovery rate is therefore a less conservative method than adjusting them for the familywise error rate, but a sensible method in cases where many p-values from many different tests need to be controlled for, such as in the present case.

### Power analyses

Power analyses were conducted on the basis of simulated data that in turn was based upon bootstrapped data from the pilot study. In the pilot study, each of the two interventions was conducted in two individual preschool units, and a third unit was used as control. Pre- and posttesting was conducted in a similar manner as in the full study. In the following, we first describe the data simulation procedure and then move on to the actual power analyses.

### Data simulation

The data used in the power analyses is based upon semi-bootstrapping. The data is based upon bootstrapped data from the pilot data set. Additional random noise is added to data in order to create a greater deal of variability between each bootstrapped cluster. Crucially, the simulation procedure allows for the specification of intervention main effects on particular dependent variables, making it possible to calculate power of intervention effects under different effect sizes.

The original pilot data set suffers from a lot of missing data, especially in the pretest data set. In particular, there is no language data available in the pretest data. Missing data was therefore interpolated on the basis of regression modelling. This was done by regressing each dependent measure on the background variables and the other dependent measures available. Regression models for each dependent measure were then selected on the basis of backward elimination. These models were then used to predict missing data points. The three language measures (number of unified predicates, number of subordinates and number of events) in the pretest data set were completely interpolated from the posttest data set in this way.

The bootstrapping procedure uses with-replacement random sampling to sample 9 clusters from each intervention group in the pilot data (i.e., 27 clusters in total), each cluster consisting of 12 children. As a result, each bootstrap sample consisted of a total of 324 children. In the bootstrapping of ERP data, cluster sizes ranged from 3 to 7 children, resulting in an average ERP bootstrap sample size of 135.

In order to increase the variation between clusters and individuals, additional random noise within the range of ±0.4 standard deviations, sampled from a uniform distribution, was added to the continuous predictor variables. For ECERS-3 scores, random noise within the range of ±0.5 standard deviations was used. All adjusted variables were trimmed so that any values lying outside the possible range of the variable at hand (e.g., 1–10 for SES) were adjusted to either the minimum or maximum value, and integer variables, such as SES, were rounded to the nearest integer.

Figure 1 illustrates the relationship between the pilot data and a bootstrapped data sample, in terms of plotting the relationship between EFScore and Age. The larger circles show the data points of the children in the pilot study (each child being colour coded), and the dots show the data points in the bootstrapped data. The dashed regression lines illustrate the linear fit between EF Score and Age in the bootstrapped data sets, and the dotted lines the linear fit between EF Score and Age in the pilot data set.

**Fig. 1 Fig1:**
[figure not shown]
The relationship between EFScore and Age in the pilot data set and a bootstrapped data set with noise adjustment set to 0.5 standard deviations. Colours differentiate between children in the original pilot data. Diamonds illustrate data points in the pilot data set and dots show bootstrapped data points. The dashed regression line illustrates the linear fit in the bootstrapped data set, and the dotted line the pilot data set

In addition to adding noise to the data, the dependent measures were adjusted for intervention main effects. This was done by adjusting the difference between the pre-, x_pre_, and post, x_post_ measurements of the aforementioned dependent measures so that they differed in strength in accordance with some adjustable effect size δ. More specifically, the mean difference between pre- and post-measurements was added to each post-measurement data point, i.e., x_post_ = x_post_ + Σx_pre_ / n_pre_ - Σx_post_ / n_post_, in order to ensure no initial difference between mean pre- and post-measurements. Then, the pooled standard deviation over interventions, σ, was calculated. Individual post-measurements were then increased in accordance with its effect size on the basis of the pooled standard deviation, i.e., x_post_ = x_post_ + δσ. Table 3 shows the effect size adjustments used for each intervention and each of the adjusted dependent measures. The table illustrates small, most likely insignificant, effects in the control intervention, strong EF effects but weak language and emotional comprehension effects in the DIL intervention, and, on the other hand, weak EF effects but strong emotional comprehension and language effects in the SEMLA intervention.

**Table 3 Tab3:** Effect size adjustment δ for each intervention and dependent measure

Dependent Variable	Control	DIL	SEMLA
DCCSScore	0.1	0.5	0.3
FlankerScore	0.1	0.5	0.3
HeadShoulders	0.1	0.5	0.3
Math	0.1	0.5	0.3
FDS	0.1	0.5	0.3
TEC	0.1	0.2	0.6
PPVT	0.1	0.3	0.5
LangPredicates	0.1	0.3	0.5
LangSubordinates	0.1	0.3	0.5
LangEvents	0.1	0.3	0.5

### Power calculations

Power was calculated for each regression coefficient in all of the models described above, in the section about statistical analysis. This was done by refitting each model on 2000 bootstrap /simulation samples, generated as described above. Power statistics were then calculated on the basis of the resulting model coefficient distributions. We calculated mean beta values and also beta confidence intervals, consisting of the 5 and 95% quantiles of each beta coefficient distribution. A beta confidence interval that spans 0 indicates that the effect at hand is non-significant. We also calculated mean *p*-values for the respective coefficients over the 2000 model fits, p-value confidence intervals, consisting of the 5 and 95% quantiles of the distribution of these p-values, as well as bootstrapped p-values, calculated on the basis of the bootstrap distributions of model coefficients. More specifically, bootstrapped p-values are the proportions between the bootstrapped coefficients that span zero and the total number of coefficients (i.e., 2000). For a coefficient C with a mean beta value > 0, boot p-values are the proportion n(C = < 0) by N(C), and for a coefficient with a mean beta value < 0, boot *p*-values are the proportion n(C = > 0) by N(C). Further, the model coefficients that are critical for the hypothesis testing (e.g., the intervention effect coefficients) were adjusted for multiple comparisons, in terms of adjusting for the false discovery rate (see above).

Finally, power was calculated as the proportion of significant p-values (assuming alpha = 0.05) to the total number of 2000 p-values. In other words, power is the percentage of times that the bootstrapped models found the coefficient at hand to be significant.

In the following, we present power analysis statistics for all models testing hypotheses corresponding to research questions RQ1 to RQ5.

### RQ1 and RQ2 analyses: Intervention effects and intervention differences

Since RQ2 hypotheses regarding intervention differences will be tested on the basis of planned comparisons testing differences between the intervention effects in the RQ1 hypothesis models, RQ1 and RQ2 analyses will be tested together. As mentioned above, we will apply p-value correction to the p-values of coefficients that address the hypotheses.

Table 4 shows the statistics for the intervention model coefficients, including the planned comparisons of the intervention differences, for all RQ1 and RQ2 models. These models test intervention effects and intervention differences on EF, Language, Math and TEC. Apart for the SEMLA intervention effect on EF score and the DIL intervention effect on TEC, these analyses’ power show strong power for all intervention effects and intervention differences under the assumed effect sizes (see Table 3). Notably, the Beta coefficient for the SEMLA intervention on math is negative, indicating that SEMLA in fact might have a negative effect on early maths skills.

**Table 4 Tab4:** Simulation statistics for the intervention model coefficients of all RQ1 and RQ2 models

Statistic	EFScore			Language Score			Math			TEC		
	DIL	SEMLA	DIL vs. SEMLA	DIL	SEMLA	DIL vs. SEMLA	DIL	SEMLA	DIL vs. SEMLA	DIL	SEMLA	DIL vs. SEMLA
Mean Beta	0.85	0.30	0.55	0.49	1.06	−0.57	0.10	−0.08	0.18	0.02	0.75	−0.73
Beta.lower	0.55	−0.03	0.22	0.21	0.78	−0.87	0.06	−0.14	0.11	−0.50	0.31	−1.18
Beta.upper	1.16	0.64	0.82	0.77	1.34	−0.28	0.13	−0.02	0.25	0.98	1.67	−0.31
boot.p	.000	.036	.000	.000	.000	.000	.000	.003	.000	.584	.002	.002
mean.p	.000	.096	.003	.008	.000	.003	.003	.029	.000	.424	.018	.022
p.lower	.000	.000	.000	.000	.000	.000	.000	.000	.000	.000	.000	.000
p.upper	.000	.774	.036	.080	.000	.033	.022	.326	.000	.971	.157	.195
Power	1.00	0.69	0.98	0.96	1.00	0.99	0.99	0.89	1.00	0.17	0.91	0.89
adj. p mean	.000	.118	.005	.010	.000	.001	.004	.038	.000	.472	.026	.031
adj. p.lower	.000	.000	.000	.000	.000	.000	.000	.000	.000	.000	.000	.000
adj. p.upper	.000	.816	.062	.130	.000	.050	.037	.408	.000	.975	.214	.252
adj. Power	1.00	0.61	0.97	0.94	1.00	0.97	0.98	0.86	1.00	0.16	0.87	0.85

